## Abstract

**Supplementary Information:**

The online version contains supplementary material available at 10.1007/s11357-023-00813-6.

## Introduction

Chronological age is the primary risk factor driving major chronic diseases, including cardiovascular disease (CVD), cancer, neurodegeneration, type 2 diabetes, sarcopenia, and osteoporosis. Geroscience research aims to understand the molecular and cellular mechanisms of aging as the main driver of chronic diseases and it has identified key biological tenets of aging, which, when targeted with drugs or supplements, result in the increased healthspan, compression of morbidity in aged animals and in some cases, the extension of lifespan [1–3]. Translation to clinical research in humans is still in its early stage. Accelerated aging results in reduced or impaired function of multiple organ systems, including the cardiorespiratory, metabolic, immune, and musculoskeletal systems. Age-related changes can be measured at the molecular, cellular levels and used as a guide for clinical interventions as the inclusion criteria and/or assessing the effectiveness of the intervention [3]**.** Among features of aging, the epigenetic modifications, changes in the genome that are not due to changes in the genetic sequence, are implicated in aging. These modifications commonly involve DNA methylation and histone modifications (including methylation and acetylation), which alter the accessibility of DNA and affect many nuclear processes including transcription [4]. Epigenetic modifications change with chronological age, responding to the environmental factors, indicating a degree of plasticity [4]. In human studies, the epigenetic load is quantifiable and can be a useful marker for measuring biological aging.

Alpha-ketoglutarate (AKG) is an intermediate of the Krebs cycle, which is involved in various metabolic and cellular pathways as a signalling molecule, energy source, and precursor of amino acid synthesis [5]. AKG is a weak acid containing two carboxyl groups and a ketone group. As a metabolite, AKG, is an antioxidant, regulates nitrogen and ammonia balance, as well as epigenetic and immune processes [6]. AKG is also a substrate for Ten-Eleven Translocation (TET) methylcytosine dioxygenases, which contribute to DNA demethylation [7]. Mitochondrial function decreases with age, which could contribute to the overall decrease in levels of AKG [8]. Several metabolites such as fatty acids, vitamins, microelements, nucleic acids, and amino acids occur naturally within cells [9, 10]. These metabolites have been identified to modulate aging, as well as exert organ-specific effects [9, 10]. Among these metabolites, AKG has been of a particular interest due to its essential role in cellular metabolism, energy production and aging. In this regard, AKG has been studied as a geroprotective agent in model animals [9, 11, 12]; in humans, the effects of AKG were tested mostly in haemodialysis and burn patients [13–20], only one retrospective study have assessed the geroprotective potential of AKG in a general population [21]. AKG can be administered alone or as salt with calcium, sodium, or ornithine [22]. Several clinical trials that used Ca-AKG in hemodialysis patients found it to be safe at doses up to 4.5 g/day, to increase plasma arginine and decrease plasma urea levels [17–20]. In post-menopausal women 6 g/day of Ca-AKG for 6 months was found to be safe and induced beneficial changes in serum levels of the bone resorption marker CTX (C-telopeptide type I collagen) consistent with the preservation of bone mass in the lumbar spine [23]. AKG reduced ischemic markers in circulation of men undergoing coronary surgery when added to blood cardioplegia for intermittent antegrade intracoronary perfusion [24]. AKG also prevented muscle atrophy in a Duchenne muscular dystrophy mouse model [25]. Thus, it appears that AKG has pleiotropic function and can affect multiple physiological systems [22]. Secondary outcomes in current study will aim to assess the effect of Ca-AKG on muscle health by functional tests (handgrip strength and 8 repetition maximum test), cardiovascular function by pulse wave velocity analysis, body composition and bone density by dual energy x-ray absorptiometry, aerobic capacity with cardio-pulmonary exercise test. Blood samples will be collected to measure inflammatory parameters, kidney function, fasting triglycerides, high-density lipoprotein, glucose, and liver profile.

In addition, the effect of Ca-AKG on the relationships of clinical and biological parameters to DNA methylation as well as a detailed profile of responders and non-responders can be studied in the post hoc analysis.

This study includes healthy participants with a higher DNA methylation age and will test whether 1 g of Ca-AKG can reduce this age.

## Methods

### Study design

This single-center, randomized, parallel, double blinded, placebo-controlled trial will investigate if 1 g/day of sustained release Ca-AKG compared to placebo can lower DNA methylation age in 120 middle-aged healthy individuals. Participants whose DNA methylation age is greater than their chronological age will be eligible for intervention.

All the participants will provide informed and written consent before the screening visit in accordance with the Declaration of Helsinki. The study has been approved by NUS IRB (NUS-IRB-2021-946) and registered at clinicaltrial.gov (NCT05706389).

### Intervention

The study is using 1 g/day of Ca-AKG sustained-release tablet (Ponce De Leon Health, USA). The placebo ingredients are listed in Supplementary Table 5. The Ca-AKG and placebo pills and bottles are identical in appearance.

### Pre-screening and screening

Potential participants who express interest will be pre-screened by email or phone call (Fig. 1), when their chronological age and health status will be confirmed. If they fit the inclusion and pre-screening exclusion criteria (Table 1), they will be invited for a screening visit. At the screening visit after signing the informed consent, the fasting blood sample will be taken to assess their DNA methylation profile, fasting triglycerides, high-density lipoprotein, glucose, and liver profile (total protein, albumin, globulin, bilirubin, alkaline phosphatase, aspartate aminotransferase). The screening will include as many participants as necessary to achieve 120 randomized participants.

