### Study visits

Eligible participants will be invited to the baseline visit when they will be randomized to receive Ca-AKG or placebo. At baseline, participants will complete the assessments, including a blood draw, saliva sample collection, anthropometry and physical assessments, carotid-femoral pulse wave velocity, body composition with dual energy X-ray absorptiometry (DXA), cardio-pulmonary exercise test (CPET), skin autofluorescence assessment and answer questionnaires including a socio-demographic survey, sleep and quality of life questionnaires, international physical activity questionnaire, global preferences survey and Montreal Cognitive Assessment test and menopause questionnaire (females only) (Table 2). Participants will receive their 3-months’ supply of Ca-AKG or placebo supplements, activity tracker (ActiGraph, wGT3X-BT), 3-day food record, physical activity diary and stool collection kit (AMILI Pte. Ltd.).

**Table 2 Tab2:** Overview of assessments and visits

Methodology	Screening	Visit 1	Visit 2	Visit 3	Visit 4
Signed informed consent	√				
Screening Checklist	√				
Clinical assessments					
Anthropometry	√	√	√	√	√
Body Composition (DXA scan)		√		√	√
Arterial Stiffness (carotid-femoral pulse wave velocity)		√	√	√	√
Cardiopulmonary exercise Test		√		√	√
Muscle Strength Tests		√		√	√
Skin Autofluorescence test		√	√	√	√
Questionnaires					
Socio-demographic Survey		√	√	√	√
Sleep Questionnaire		√	√	√	√
SF-36 Questionnaire		√	√	√	√
EuroQoL-5D-5L		√	√	√	√
MoCA		√	√	√	√
IPAQ		√	√	√	√
Menopause Questionnaire	√	√	√	√	√
3-day food diary		√	√	√	
Physical activity diary		√	√	√	√
Global Preferences Survey		√		√	
Blood parameters					
DNA methylation	√	√	√	√	√
Complete blood count	√	√	√	√	√
Fasting lipid panel	√	√	√	√	√
Fasting glucose	√	√	√	√	√
Fasting haematological panel	√	√	√	√	√
Fasting protein panel	√	√	√	√	√
Renal Function test	√	√	√	√	√
Insulin & HbA1C		√	√	√	√
Metabolite concentrations		√	√	√	√
Inflammatory markers		√	√	√	√
Other samples and assessments					
Saliva Samples		√	√	√	√
Stool Samples		√	√	√	√
Activity Tracker		√	√	√	√

Three months, 6- and 9-months visits (Fig. 1) include assessments as described in Table 2. At 3 months visit the participants will bring back the bottles (empty or with unused supplements) and will also receive the new 3-months’ supply of Ca-AKG or placebo.

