### Anthropometry, body composition, physical assessments, and activity tracking

Height will be measured with a stadiometer (SECA217, SECA Gmbh&Co KG, Germany) and weight will be measured with a floor weighing scale (SECA813, SECA Gmbh&Co KG, Germany). Body mass index (BMI) will be calculated. Waist and hip circumference will be measured three times with a cloth measuring tape (SECA201, SECA Gmbh&Co KG, Germany), at the level of the umbilicus (waist) and at the level of the symphysis pubis and the greatest protrusion of the gluteal muscle (hip). Body composition and hip and lumbar bone mineral density will be measured by the DXA machine (Horizon DXA system, Hologic, Inc., USA). Body composition is being expressed as body fat mass in % and kg, lean muscle mass in % and kg with the fast array mode as listed in Supplementary Table 1.

For the handgrip strength measurement, the participant will hold the dynamometer (Jamar Plus + , Sammons Preston Rolyon, USA) in a standing-handshake position [33]. The participant will squeeze the handle of the dynamometer with maximum effort. The test will be conducted three times on both arms, with 1 min rest between each attempt [34].

Participants will perform the 8-repetition maximal (8-RM) leg extension on a seated leg extension machine (640 LEC, GYMSPORTZ, Singapore), with the initial weight of 10 kg. If the participant is able to perform 8 repetitions, without being able to do the 9th repetition, the weight will be recorded as 8-RM strength. If the participant is able to do 9 repetitions for the given weight, the rate of perceived exertion (RPE) will be measured after every set, to determine the amount of next incremental load, to be added after every set, with a rest period of 5 min, until 8-RM is achieved (Supplementary Table 1). For a validated repetition, a complete range of motion has to be performed.

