### Cardiopulmonary exercise test

Participants will perform a graded maximal treadmill walking depending on their initial fitness level. The purpose of this assessment is to determine participant’s maximal aerobic capacity; thus, the test will be stopped when the volume of oxygen peak (V̇O_2peak_) is achieved or if the participant is unable to continue for any reason. Ten minutes of rest prior to the test will allow to capture baseline physiological parameters such as heart rate, V̇O_2_, the volume of carbon dioxide expired (V̇CO_2_), pulmonary ventilation during exercise (V̇E), respiratory exchange ratio (RER), excess post-exercise oxygen consumption (EPOC), heart rate recovery, and aerobic and anaerobic recovery thresholds [37] (Supplementary Table 1). After 3 min of warm up at 3 km/h, the speed will be increased to 6 km/h at 0% incline. The treadmill elevation will be increased by 3% every 3 min without changing the speed until volitional fatigue is achieved by the participant. The maximum inclination of the treadmill is set at 21. Rate of perceived exertion (RPE) will be measured at baseline, as well as ~ 30 s before the end of each stage and immediately after the exercise testing. Lactate (mM) and glucose (mM) will be measured from the fingertip capillary blood at baseline and immediately after the exercise testing.

V̇O_2_peak is determined with the following criteria(s): respiratory exchange ratio (RER) ≥ 1.15 and/or blood lactate: ~  + 8 mM above resting values and/or heart rate: ~ 100% of age-predicted HR max/HR reserve and/or RPE of > 17 and/or V̇O_2_ plateau (< 2.1 ml/min/kg in V̇O_2_ despite increase in workload) and/or volitional fatigue [38].

After completion of the exercise, the same physiological variables as in the beginning of the test will continue to be measured during the 30 min of recovery for determining the recovery parameters (Supplementary Table 1).

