### Sample collection, analysis and biobanking

Fasted blood will be collected at screening, baseline, 3, 6, and 9 months (Table 2). Buffy coats from the blood samples will be used for DNA methylation. Blood variables during visits 1 to 4 will include the same measurements as the screening visit parameters and insulin (mIU/L), HbA1c (mmol/mol), metabolite concentration (Nightingale Health Plc, Finland), circulating immune and inflammatory markers (Olink, Sweden) (Table 2). Peripheral blood mononuclear cells will be isolated by Ficoll gradient centrifugation (Ficoll-paque, Cytiva, USA) and stored for immunophenotypic analysis (Supplementary Table 2). Any excess blood samples in the form of plasma, serum, frozen buffy coats will be stored for future analysis if the participants consented for it, including participants who do not meet the inclusion criteria after screening.

Fasted saliva samples will be collected from participants in a seated position, where they will passively drool into a collection tube (Isohelix, Kent, UK) pre-filled with guanidine-free, DNA stabilization buffer. Samples will be immediately placed on ice and stored at − 80 °C. Genomic DNA from saliva will similarly be extracted with QIAamp® DNA Mini kits and these samples will be used for genome-wide DNA methylation analysis using the EPIC BeadChip. This will be compared with the results obtained from the blood DNA methylation analysis, aiming to study the association of both tests. The second saliva collection tube will be immediately frozen for future analysis (Supplementary Table 2).

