### Safety assessments

Ca-AKG is Generally Recognized As Safe (GRAS), thus, no adverse events are expected to be related to the effect of Ca-AKG. However, documentation of all adverse events reported by participants will be recorded. All serious adverse events will be reported to the ethics committee (NUS-IRB) and to Health Science Authority of Singapore within 24 h. In addition, to ensure safety, liver function, kidney function, and complete blood test will be done at 3, 6, and 9 months.

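### The only liver panel the article defines has AST as its sole transaminase, so the liver safety draws would measure neither ALT nor any muscle enzyme

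*Protocol article*

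**What the plan says.** Four places in the protocol article bear on liver testing.

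- **Pre-screening and screening** gives the content of the panel: "liver profile (total protein, albumin, globulin, bilirubin, alkaline phosphatase, aspartate aminotransferase". That is six analytes, with no wording to mark them as examples.
- **Sample collection, analysis and biobanking** carries it forward: "Blood variables during visits 1 to 4 will include the same measurements as the screening visit parameters". The additions it then names are insulin, HbA1c, metabolites, and immune and inflammatory markers. None is a liver enzyme.
- **Safety assessments** gives the purpose and timing: "to ensure safety, liver function, kidney function, and complete blood test will be done at 3, 6, and 9 months". It does not say which analytes make up liver function.
- **Study visits, Table 2** has no row for liver enzymes. The nearest is "Fasting protein panel", ticked at screening and at Visits 1 to 4.

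The Introduction also names the liver profile among the blood measures it lists alongside the secondary outcomes.

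The same participants do strenuous tests. The treadmill protocol continues "until volitional fatigue is achieved by the participant", and the strength assessment includes an 8-repetition maximum leg extension. Table 2 ticks the treadmill test and the row "Muscle Strength Tests" at Visits 1, 3 and 4.

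**The concern.** AST is released from skeletal muscle as well as from liver, so on its own it is a weak guide to the liver. The usual companion is ALT, which is more specific to the liver. With ALT missing and no muscle enzyme measured, two things can go wrong for an individual participant. A raised AST with normal bilirubin and alkaline phosphatase leaves the safety reviewer unable to say which tissue it came from. And injury to liver cells that shows mainly in ALT would not be seen at all.

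This matters because the article expects no product-related adverse events and otherwise records the events that participants report. The laboratory tests are therefore the main objective safety check, and the liver panel is one of the three named.

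**Working it through.** The article states no figure on this point, so the check is a reading of the passages together, plus a count.

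**1. Content of the panel.** Six analytes are listed (Pre-screening and screening). Transaminases: one (AST). ALT: none. Muscle enzymes: none. ALT, gamma-glutamyl transferase and creatine kinase do not appear anywhere in the text shown.

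**2. Where the panel applies, and where the exercise tests fall** (sample collection section, Safety assessments, Table 2):

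| Visit | Liver profile | Named safety draw | Treadmill and strength tests |
|---|---|---|---|
| Screening | yes | no | no |
| 1 (baseline) | yes | no | yes |
| 2 (3 months) | yes | yes | no |
| 3 (6 months) | yes | yes | yes |
| 4 (9 months) | yes | yes | yes |

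**3. Number of panels.** With 120 randomized participants and full attendance, the named safety draws give 120 x 3 = 360 panels. This is an upper bound on panels, not an estimate of missed signals. The article describes product being handed out at baseline and at 3 months, each time for three months. If that is the whole supply, 120 x 2 = 240 of these panels fall during supplementation and 120 after it.

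**4. Could the trial's own exercise tests raise AST?**

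- Earlier visits: the last exercise tests before the 3-, 6- and 9-month draws are at baseline, baseline and 6 months, so the gaps are about 3, 6 and 3 months. Carry-over over such gaps is not a credible explanation.
- Same visit: this is possible only at 6 and 9 months, in up to 120 x 2 = 240 panels, and only if blood is taken after the exercise. The draws are fasted, and Study visits names the blood draw first among the baseline assessments, but no section fixes an order.

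The exercise tests are therefore a possible source of disturbance, not a demonstrated one. A participant's own exercise outside the trial can still raise AST before any draw.

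**5. Effect on the comparison of arms.** The trial is randomized and double-blind, and both arms follow the same schedule. AST of muscle origin adds noise to both arms and does not by itself create a difference. The loss is in reading individual values and in not measuring ALT.

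**The case against.** The strongest objection is that the list need not be complete. The account of screening bloods in Pre-screening and screening leaves out the complete blood count, the haematological panel and the renal function test, all ticked at screening in Table 2. The sample collection section says that the visit bloods include the screening measurements, which does not exclude others. Safety assessments names no analytes, and an article may leave an itemised laboratory list to the full protocol. This makes the closed reading less certain. It does not remove the point: the article chose to itemise this panel, and nothing shown adds ALT to it. If the full protocol does include ALT, the published list is incomplete and should be corrected.

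A second objection is that the product is described as generally recognised as safe, and that 6 g/day for 6 months was reported safe in post-menopausal women, against 1 g/day here. That lowers the chance of a liver signal. But the plan itself undertakes to monitor liver function for safety, so the panel should be able to do that job.

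Third, the article does not say that AST also comes from muscle. That is correct, and the point depends on this general laboratory knowledge.

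A reader might also infer that the maximal exercise tests confound the liver results, so that the arms cannot be compared. The article does not support this: it does not say that blood follows exercise, there is no exercise test at 3 months, both arms do the same tests, and bilirubin, alkaline phosphatase and albumin are also measured. Nor does it make this panel the check on the liver criteria in Table 1. Hepatitis and cirrhosis are pre-screening exclusions, handled by email or phone before blood is taken, and fatty liver is listed with no enzyme threshold.

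**Conclusion.** The point holds in a limited form. The only liver panel that the article defines has AST as its sole transaminase, and that panel is carried to the visits at which liver function is meant to protect participants. As written, up to 360 post-baseline safety panels would include no ALT and no muscle enzyme. An isolated AST rise would be hard to attribute in an individual, and injury showing mainly in ALT would be missed.

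A reader might count all five draws, 120 x 5 = 600, as safety panels. Safety assessments names only three, and screening and baseline come before treatment.

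The conclusion rests on three assumptions: that the itemised list is the one used at Visits 1 to 4, that no undisclosed document adds ALT, and that AST is less liver-specific than ALT. The primary outcome is not affected, and no bias between arms is claimed. It is a modest weakness in safety monitoring that is cheap to remove.

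**What to change.** 1. Add ALT to the liver profile in Pre-screening and screening, run on the existing fasting samples at screening and, through the carry-over sentence, at Visits 1 to 4.
2. Name the same liver analytes in Safety assessments, and give Table 2 a liver-enzyme row.
3. State in Study visits that blood is drawn before that visit's treadmill and strength tests.

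If the full protocol already includes ALT, only the wording changes are needed.

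**Cost:** one routine assay per existing sample. With full attendance that is 120 x 5 = 600 assays in randomized participants, plus one for each person screened but not randomized. No extra visit or blood draw is needed.

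**Limit:** ALT makes an isolated AST rise easier to read, but without a muscle enzyme it does not fully settle whether the source is liver or muscle.

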**Fig. 1 Fig1:**
[figure not shown]
ABLE study schedule. Pre-screening of interested individuals is done by email or phone. At screening consent is taken followed by blood sample for checking the screening criteria. Eligible participants are invited for baseline visit when the randomization happens. They will come back at 3 months, 6 months, and 9 months to complete all the assessments

**Table 1 Tab1:** Inclusion and exclusion criteria

Inclusion criteria	Pre-screening exclusion criteria *any condition*	Screening exclusion criteria > *1 condition*
40–60 years of age	Any cardiovascular disease, severe / uncontrolled hypertension, rheumatic heart disease, congenital heart disease, deep vein thrombosis, pulmonary embolism	Waist circumference ≥ 90 cm (males) ≥ 80 cm (females)
DNA methylation age > chronological age	Type 1 / 2 diabetes (oral metformin or insulin therapy), diabetic complications	Fasting triglycerides ≥ 1.7 mmol/l
	Active cancer or on treatment in the last 3 years	High-density lipoprotein < 1.0 mmol/l (males); < 1.3 mmol/l (females)
	Chronic obstructive pulmonary disease (COPD), severe asthma (daily medications)	Blood pressure ≥ 130/85 mmHg or use of antihypertensive medication
	Multiple sclerosis, autoimmune/immune deficiency diseases	Fasting glucose ≥ 6.0 mmol/l
	Recent history of sepsis or infection (hospitalization in last 3 months)	Osteopenia
	Any psychiatric disease or neurodegenerative diseases	Mild Osteoarthritis not interfering in daily activities
	Any metal implants in the body	Fatty liver
	Hepatitis / Liver cirrhosis	
	Severe kidney disease (GFR < 30 ml/min/1.73 m^2^)	
	Skin disease (oral medication)	
	On other investigational product within 60 days or 5 half-lives before the screening	
	Any serious medical illness (PI’s judgment)	
	Pregnant women or planning pregnancy in the next 9-months	

